### Trial status

Phase 1 of this study, measure development, is nearly complete. Both design and advisory teams were formed to develop and evaluate the objectives, indicators, and contingencies. These development meetings are complete; we are now finalizing the specific data sources for the indicators developed, which will be used to prepare the feedback reports in phase 3. The core study team is currently in phase 2 of the study and preparing for phase 3. We have modified our control arm sampling strategy from all available PACTs at two VISN 12 sites to a random sample of PACTs from anywhere in VISN 12 to minimize contamination.

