### Project description and study design

This project consists of three phases: (1) developing measurable, prioritized point-of-care criteria for effective PACT coordination, to be accomplished using ProMES (detailed below); (2) identifying the specific information needed at the point of care to improve coordination and recommend point-of-care aids for delivering the needed information, to be accomplished via focus groups with the phase 1 participants; and (3) assessing the effect of adopting the aforementioned coordination standards and point-of-care aids on PACT clinicians’ coordination behaviors.

Phase 3 consists of a trial with two arms: (1) a concurrent control arm drawn randomly from PACTs which will be monitored passively and (2) a measurement and feedback arm (two sites from a single regional network), which will be involved in designing the coordination measures and identifying the point-of-care aids and will receive periodic feedback on their coordination performance. The design of the three phases of the study is summarized in the flow chart in Fig. 1. Each phase is discussed below in detail.

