### Procedures

#### Begin measuring coordination

Upon completion of phase 1, we will begin securing the necessary permissions to obtain the data required for generating the indicators developed during phase 1. Subsequently, measurement of PACT coordination will begin at all four sites, using the measures developed in that aim. The period between completion of phase 1 and identification of point-of-care aids will serve as a baseline; during this period, we will provide no feedback, only passively monitor coordination.

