## Phase 3: assess the effect of adopting the aforementioned coordination standards and point-of-care aids on PACT clinicians’ coordination behaviors

### Design and site selection

Our study will take place at four facilities within Network 12 with a high degree of alignment with PACT. Within this subset, we will select sites based on geography (rural vs. urban) and size (CBOC vs. VAMC) to ensure maximum variation; we will approach sites uninvolved in other projects from this CREATE to ensure an uncontaminated study design.

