### Participants

For this phase, we will recruit members of all available PACTs at the four Network 12 study sites. Given our site selection criteria, we estimate each study arm will have an average of approximately 152 members clustered into 28 PACTs. For purposes of informed consent, we will treat all PACT members at a site as study subjects; we are aware that not all PACT members may consent to participate; however, our intervention is an intent-to-treat design, and the unit of analysis is the PACT, not the individual PACT member (our outcome of interest, coordination, is by definition a collective construct). Consequently, as long as at least the provider of a given PACT consents, we will include that PACT’s data in our analyses, taking into consideration the limitations of that PACT’s data.

Optimal design software developed by Raudenbush and colleagues [28] was used to calculate the estimated effect size for varying levels of power for a multilevel cluster randomized trial with repeated measures. With a two-tailed alpha of 0.05 and 6 sites with an average of 10 PACTs per site, an intra-class correlation coefficient for sites of 0.02 (estimated from prior VA data), and approximately 12 repeated assessments, we have 80 % power to detect a medium-to-large effect size (*δ* = 1.13) and 87 % power to detect a large effect (*δ* = 1.25). Pritchard and colleagues’ [19] meta-analysis examining the effectiveness of ProMES as improving productivity found a large overall effect size (*δ* = 1.44); accounting for moderators, effect sizes were as high as 2.21. Thus, we should be able to adequately detect improvements using the proposed number of PACTs.

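### The network-wide control draw drops the site criteria set for study sites, so the arms come from different frames without random allocation, and a selection-linked trend could pass for an intervention effect or hide one

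*Protocol article*

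**What the plan says.** All references are to the protocol article.

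- **Phase 3, Design and site selection.** The study is placed at "four facilities within Network 12 with a high degree of alignment with PACT". Sites are varied on rural/urban and CBOC/VAMC, and "we will approach sites uninvolved in other projects from this CREATE to ensure an uncontaminated study design".
- **Phase 3, Participants.** "we will recruit members of all available PACTs at the four Network 12 study sites", with about 28 PACTs per arm. The power calculation assumes a cluster randomized trial.
- **Phase 2, Begin measuring coordination.** "measurement of PACT coordination will begin at all four sites".
- **Project description and study design.** The intervention arm is two sites that help design the measures. The other arm is "a concurrent control arm drawn randomly from PACTs which will be monitored passively".
- **Trial status.** The control arm has been changed "from all available PACTs at two VISN 12 sites" to "a random sample of PACTs from anywhere in VISN 12 to minimize contamination".
- **Phase 3, Data analysis.** Improvement between the baseline and performance periods is compared across arms by growth curve modeling. Time point and study arm are the predictors named. A steeper intervention slope supports the hypothesis.

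**The concern.** Before the change, both arms came from sites that passed the same screen. The change affects only the control arm, and the new description does not repeat the screen. The intervention arm still consists of sites chosen for high PACT alignment and for having no other project of this CREATE. The controls are a random draw from a network of seven medical centers and over 30 clinics.

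Random sampling makes the controls representative of the network. It does not make them comparable with two selected sites. If PACTs at high-alignment sites improve at a different pace for reasons unrelated to feedback, the planned slope comparison would attribute that difference to the intervention, or would lose a real effect behind it.

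There is also a conflict of purpose. Design and site selection keeps the design uncontaminated by avoiding sister-project sites. Trial status lifts the only stated restriction on where controls may sit, and does so to reduce contamination.

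**Working it through.** The plan gives no figure on this point, so the check is mainly a comparison of its sections, followed by an illustration.

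**1. Sampling frames side by side**

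| | Intervention arm | Control arm (current) |
|---|---|---|
| Unit chosen | Two whole sites | Individual PACTs |
| High PACT alignment | Required | Not stated |
| Outside other projects of this CREATE | Sought | Not stated |
| Rural/urban, CBOC/VAMC | Used in site selection | Not stated |
| Intervention sites excluded | Not applicable | Not stated |
| Random allocation to arm | Not described | Not described; random sampling only |

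With whole sites as one arm and a network-wide sample of PACTs as the other, the design as described is not the cluster randomized trial assumed for power.

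**2. Which sections agree**

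Trial status and Project description and study design agree on a random draw. The four-site wording in Phase 2 (Begin measuring coordination) and in Phase 3 (Design and site selection; Participants) fits the superseded arrangement of two intervention sites plus two control sites.

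**3. What the analysis removes and what it leaves**

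Let the arms differ before intervention by a level difference L, and let PACTs improve between periods by different amounts for reasons of site selection, the difference being b. Comparing change from baseline cancels L. The estimated effect is then (true effect + b). With time point and study arm as the only named predictors, nothing in the model separates b from the intervention.

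**4. Illustration of size**

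Inputs: 28 PACTs per arm and site ICC 0.02 (Participants). The ICC was given for the power calculation and is borrowed here for improvement. Assumptions not in the documents: b in units of the SD of PACT-level improvement, no true effect, and a two-sided 0.05 z test.

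- Ignoring clustering: SE = √(2/28) = 0.267.
- Two intervention sites of 14 PACTs each, controls treated as unclustered: SE = √[(1 + 13 × 0.02)/28 + 1/28] = √(2.26/28) = 0.284. The test is assumed to use this SE.
- Rejection probability = 1 − Φ(1.96 − b/SE) + Φ(−1.96 − b/SE).

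| Assumed b (SD) | No clustering | ICC 0.02 in the two intervention sites |
|---|---|---|
| 0 | 5.0% | 5.0% |
| 0.1 | 6.6% | 6.4% |
| 0.2 | 11.6% | 10.8% |
| 0.3 | 20.2% | 18.4% |
| 0.5 | 46.5% | 42.1% |

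Worked case: for b = 0.3 without clustering, b/SE = 0.3/0.267 = 1.12, giving 1 − Φ(0.84) + Φ(−3.08) ≈ 0.202.

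The table is symmetric in the sign of b. A positive b yields mostly false findings of benefit. A negative b subtracts from a real benefit.

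**The case against.** The strongest reply is that Trial status is one condensed sentence in an article. It does not say that the site criteria were abandoned, and a fuller document may define the frame. That is fair as far as intent goes. But the article sets the criteria for study sites in one place and describes a draw from anywhere in the network in another, so the two need reconciling.

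A second reply is that the primary comparison uses change from baseline. This stands for stable level differences. It would also stand for a constant pre-existing trend difference if the model estimated the baseline trend and tested the change in slope. It would not cover a trend that differs only during the performance period, for example through a sister project or a ceiling.

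A reader might also infer four stronger things that the documents do not support:

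- **That sampled controls have no baseline.** Phase 2, Design plans baseline data at the sites intended for phase 3, and Phase 3, Begin measuring coordination covers all study sites. Only the count of four appears out of date.
- **That controls will be drawn from the intervention sites.** This is not excluded, but it is not stated either. All available PACTs at those sites are to be recruited, which leaves few or none to sample.
- **That alignment is the main driver of the outcome.** The Background says only that coordination is among the most critical PACT principles. That makes a link plausible, no more.
- **That controls will receive a rival intervention, or that every competing project was screened out.** The criterion covers only this CREATE, and the article does not say which sites host its other projects or what those projects do.

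**Conclusion.** The point holds in limited form. As written, the arms are drawn from different frames: the criteria set for study sites are not carried over to the controls, and no random allocation is described. The wording admits controls at sister-project sites, against its own aim. The section on potential challenges and limitations does not mention that the arms may not be comparable.

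The remaining threat is a trend difference linked to site selection. Such a difference is plausible because PACT was a recent transition and sites of higher and lower alignment may be at different stages. The documents do not give its size or its direction: high-alignment sites could improve faster, or could be near a ceiling and improve less. The error rates of 6% to 47% for gaps of 0.1 to 0.5 SD therefore show sensitivity to an assumption. They do not estimate this trial's error rate. The point should be settled before phase 3 starts, but it does not show that the result will be biased.

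**What to change.** 1. Define the control frame as PACTs at network sites that are outside other projects of this CREATE and meet the alignment criterion in Design and site selection, excluding the two intervention sites.
2. If too few sites qualify on alignment, keep the other restrictions and adjust for alignment instead, including its interaction with time. This is weaker than restriction, because both intervention sites lie at the high end.
3. Stratify the draw by rural/urban and CBOC/VAMC. Put these factors and their interactions with time in the growth model, because main effects adjust level and not slope.
4. Confirm that sampled controls have baseline data over the same calendar period as the intervention PACTs.
5. Reconcile the four-site wording in Phase 2 (Begin measuring coordination) and Phase 3 (Design and site selection; Participants) with Project description and study design and with Trial status.
6. State that the arms are not randomized, and limit the conclusion accordingly.

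The cost is a smaller control frame, possibly more control PACTs per site, and a few extra model terms. The article does not say how many sites would qualify, so that count should be checked first. Phase 3 is still being prepared, so the frame can be changed cheaply now. It cannot be repaired once the controls are drawn and followed.

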## Discussion

### Potential challenges and limitations

This project faces several potential challenges and limitations. First, the research team and the participant team are geographically dispersed. This creates challenges for participatory action research, training, and for effective communication. Virtual meetings and training strategies will be critical. Second, the availability of clinical participants can be limited in many circumstances. In these cases, the design team and advisory team meetings may not have diverse representation of every role in the PACTs. Third, given the size of Network 12 and the availability of the clinicians, it is impossible for us to have representations from all the PACTs. This may limit the generalizability of the coordination measures identified and deemed acceptable by the teams.

### Contributions to science and practice

This project will materially contribute to both the science and practice of care coordination in several ways. Because of its partnership-based design, this project is in some respects a special case of a type 1 hybrid implementation trial: it evaluates the *effectiveness* of the feedback intervention tested in phase 3 but incorporates elements in all three phases that allow us to adapt and tailor the *implementation* of the intervention to our partners’ needs. Upon completion of the project, our partners will have practical, feasible, and prioritized behavioral measures of care coordination in PACT settings, which in conjunction with regular feedback, can help PACTs pinpoint areas for improvement. These measures have the added benefit of potential for adoption beyond the borders of our operational partner. In addition, PACTs will have tangible aids at the point of care to help them coordinate more smoothly, and thereby, provide better quality of care. This project also contributes to science by identifying elements of coordination that are important regardless of clinical condition or disease, thereby helping to unify the currently fragmented literature on care coordination and team-based care. Finally, the methodology we propose to use to develop the aforementioned measures, ProMES, will be used for the first time not simply as the performance measure development tool for which it is originally intended but rather as an implementation intervention to aid in identifying the interventions needed to improve coordination. By using ProMES to systematically identify the indicators of good coordination, point-of-care coordination information needs become self-evident. This innovative use of ProMES also marks a contribution to both implementation science and management science more broadly.

## Abbreviations

CHF: congestive heart failure
PACTs: Patient Aligned Care Teams (known outside the VA as the Patient Centered Medical Home)
ProMES: Productivity Measurement and Enhancement System
VA: Department of Veterans Affairs
Network 12: Veterans Integrated Service Network 12
